#### Inclusion criteria

Volunteers who meet the following criteria modified from the Headache Classification Subcommittee of the IHS will be recruited: (1) headache originating from the neck and perceived in one or more regions of the head and/or face; (2) clinical, laboratory, and/or imaging evidence of a disorder or lesion within the cervical spine or soft tissue of the neck known to be a valid cause of headache; (3) clinical signs implicate a source of pain in the neck, and the headache can be attributed to the neck disorder or lesion; (4) aged from 18 to 70 years, both males and females; (5) have not received any treatment within 2 weeks; (6) willing to abide by and sign informed consent.

#### Exclusion criteria

Volunteers who meet any of the following criteria will be excluded: (1) headache related to tumor, cervical vertebral tuberculosis, spinal canal occupying lesions, or scoliosis or resulting from intracranial infection, cerebroma, subarachnoid hemorrhage, or other diseases; (2) have had operation for cervicogenic headache; (3) serious underlying diseases of important organs such as heart, liver, kidney, brain, or blood vessels, hematopoietic disorders or diabetes; (4) pregnant or lactating women; (5) unable to understand or record scoring indicators; (6) serious mental disorder, anxiety, or depression; (7) have received other treatment or involved in other clinical trials.

#### Dropout criteria

Patients who are unable to comply with this study and fail to achieve the expected efficacy, or who experience severe changes in their condition during treatment, will be dropped from the study.

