### Interventions

Patients in the *jin* acupuncture group will receive 12 sessions of acupuncture during a period of 4 weeks, implemented by finding the *gather* and *knot* of positive reaction, the points of both stress concentration and neurogenic stimulation in cervical extensor muscles according to TCM *jin* theory and modern biomechanical principles of soft tissue. Sterile and disposable filiform needles (Suzhou Acupuncture & Moxibustion Appliance Co. Ltd. Jiangsu, China) 40 mm in length and 0.30 mm in diameter will be inserted in accordance with the permissible depth and angle of the affected side acupoints until the *de qi* sensation is achieved. Meanwhile, acupuncture techniques of lifting-thrusting and twirling-rotating will be implemented to facilitate the arrival of *qi* involving a sensation of aching, numbness, heaviness, or distension around the acupoints. The needles will be retained for 25 min and stimulated every 8 min intermittently, with each acupoint being stimulated for 10 s. Participants in the pseudo acupuncture group will receive the sham acupuncture using filiform needles on points 5 cm apart away from the acupoints used in the *jin* acupuncture group. The skin will be punctured without any manipulation and stimulation for 25 min to avoid the *de qi* sensation, with the same sessions and courses as the *jin* acupuncture group. The baseline period is 0 to week 1 with one evaluation time before participating. The course of treatment and observation period will be three sessions a week totaling 12 sessions during the course. After 4 weeks of treatment, we will provide one evaluation session. The follow-up evaluation will be performed in the eighth and sixteenth weeks. The study schedule is shown in Fig. 2; the treatment details for each group are listed in Table 1.

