### Adverse events

Any possible AEs related to acupuncture intervention that occur, including nausea, fainting, subcutaneous hemorrhage, local infection, stuck needles, or needle breakage will be checked and treated. Details of AEs will be recorded in the CRF by the acupuncturist and security administrator. Severe AEs will be reported to the Ethics Committee and DMC, and compensation will be considered if necessary. Patients who are unwilling to persist with the treatment will be removed from the trial.

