### Statistical analysis

All of the data will be entered in the CRFs and input into the database by two independent researchers, calculated by means of the SPSS 25.0 software package. Data analysis and comparison will be performed based on the intention-to-treat (ITT) population and the per protocol (PP) population, contributing to the integrity and objectivity of this study. The ITT population consists of all participants who have been randomized and received at least one session of acupuncture after the baseline. PP refers to the patients who have completed the study and did not violate the protocol. A two-sided value of *P* < 0.05 will be defined as the statistical significance, categorical variables in two groups will be analyzed by chi-squared or Fisher’s exact test, normally distributed data will be analyzed by Student’s *t* test, and non-normally distributed data by the Mann-Whitney *U* test. Continuous variables in two groups including primary outcomes (the PainVision and SEMG parameters) and secondary outcomes will be compared using a general linear model with repeated measurement methods at all time points.

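### The removal rules end study participation, not only treatment, for reasons linked to outcome, while the same patients stay in the ITT population analysed at all time points

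*Protocol article*

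**What the plan says.** Two sections of the protocol article take patients out of the study.

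- **Dropout criteria.** The first trigger is "Patients who are unable to comply with this study and fail to achieve the expected efficacy". The second covers patients "or who experience severe changes in their condition during treatment, will be dropped from the study".
- **Adverse events.** "Patients who are unwilling to persist with the treatment will be removed from the trial".

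The Statistical analysis section defines two populations. The wider one is given as follows: "The ITT population consists of all participants who have been randomized and received at least one session of acupuncture after the baseline". The narrower one, for the second analysis, is restricted to completers without violations: "PP refers to the patients who have completed the study and did not violate the protocol". Continuous outcomes, including the primary PainVision and SEMG parameters, are to be "compared using a general linear model with repeated measurement methods at all time points".

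Assessments are set at baseline, at week 4 when treatment ends, and afterwards: "The follow-up evaluation will be performed in the eighth and sixteenth weeks". The primary outcomes are to be evaluated at weeks 4, 8 and 16.

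**The concern.** A patient removed under either section has been randomised and will usually have had at least one session, so belongs to the ITT population. The removal rules nevertheless take that patient out of the study itself, and neither section says that assessment continues afterwards. Membership of the ITT population is kept while the data that give it meaning are lost.

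The loss is unlikely to be random. Lack of efficacy is part of one trigger and a severe change in condition is another. Unwillingness to continue can also follow from a poor response or an adverse event. If the arms differ in outcome, they may differ in who is removed, and the comparison of those who remain no longer has the protection of randomisation. An analysis plan can choose a method for missing values, but it cannot recover measurements that sites were told to stop taking.

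**Working it through.** **1. The rules side by side**

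| Rule | Removed from | Related to outcome? | In ITT population? | In PP population? |
|---|---|---|---|---|
| Non-compliance and lack of expected efficacy | study | yes, in part | yes, after one session | no |
| Severe change in condition | study | yes | yes, after one session | no |
| Unwilling to continue treatment | trial | possibly | yes, after one session | no |

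The contradiction does not depend on any calculation: the ITT population is wider than the PP population by exactly the patients whose later data the removal rules cut off.

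**2. Which visits are lost**

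No efficacy assessment is scheduled between baseline and week 4. If expected efficacy is first judged at week 4, that value exists and weeks 8 and 16 are lost. If removal comes during treatment, all three are lost.

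**3. How much selective loss could matter (illustration only)**

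The article gives no planning values for PD, PR or SEMG, so this uses the VAS.

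- From the sample size section: means m = 2 (jin) and 4 (pseudo), true difference 2.0, 83 per arm, 10% loss allowance.
- Assumed: normal outcomes, SD s = 2.5, removal with probability p when VAS is 5 or more, and means taken over those who remain.

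With z = (5 − m)/s, and φ and Φ the standard normal density and distribution function:

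- proportion lost: L = p × [1 − Φ(z)]
- mean of those remaining: m − p × s × φ(z)/(1 − L)

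Jin: z = 1.2, φ = 0.1942, 1 − Φ = 0.1151. Pseudo: z = 0.4, φ = 0.3683, 1 − Φ = 0.3446.

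*p = 0.5*
- Jin: L = 0.0575; mean = 2 − 0.5 × 2.5 × 0.1942/0.9425 = 1.742
- Pseudo: L = 0.1723; mean = 4 − 0.5 × 2.5 × 0.3683/0.8277 = 3.444
- Difference = **1.70**

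*p = 1*
- Jin: L = 0.1151; mean = 1.451
- Pseudo: L = 0.3446; mean = 2.595
- Difference = **1.14**

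*Literal reading of the first trigger:* only non-compliant patients can be removed for lack of efficacy. If 30% are non-compliant independently of outcome (assumed), p = 0.3. Losses are 3.5% and 10.3%, the means are 1.849 and 3.692, and the difference is **1.84**. Removals under the other two triggers would add to this.

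**4. Sensitivity to the assumed SD (cut-off 5)**

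| SD | p = 0.5 | p = 1 |
|---|---|---|
| 2 | 1.72 | 1.26 |
| 2.5 | 1.70 | 1.14 |
| 3 | 1.70 | 1.07 |
| 5 (the plan's value) | 1.73 | 0.92 |

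**5. Direction**

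The acupuncturist is told the assignment, and the article does not say who decides on removal. If the rule were applied in the jin arm only (p = 0.5, SD 2.5), the difference would be 4 − 1.742 = **2.26**, above the true 2.0. So bias can go either way.

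**6. The 10% allowance**

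At p = 0.5 and SD 2.5, about 83 × 0.0575 = 4.8 and 83 × 0.1723 = 14.3 patients are lost. That is 19.1 of 166, or 11.5%, close to the allowance. The problem is which patients are lost more than how many; an inflated sample size does not correct selective loss.

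**The case against.** Several objections have weight.

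- **A reader might infer that non-response alone leads to removal.** The sentence joins non-compliance and lack of efficacy with 'and', so read literally it does not. This stands. The wording may be loose, but then the defect is ambiguity. Under the literal reading efficacy still matters: of two equally non-compliant patients, the one doing badly is dropped and the one doing well is kept. Severe change in condition is a separate trigger.
- **A reader might infer that an ITT analysis cannot be done.** The documents do not support that. The population is defined, removed patients belong to it, and an analysis plan that is not shown may specify imputation or another method. What cannot be done is an ITT analysis on observed outcomes for these patients.
- **Week-4 data may exist.** This also stands, as no earlier efficacy assessment is scheduled.
- **A condensed article need not describe follow-up after withdrawal.** Silence alone would be no finding. Here, however, the article states a rule, in two places, that participation in the study or trial ends.
- **Unwillingness to continue treatment is not selection on efficacy, and such patients may refuse visits too.** Some will, and their consent governs. The rule as written also removes those who would have attended.
- **The illustration is artificial.** It uses a secondary outcome and an invented cut-off and removal probability. It also uses an unbounded normal distribution: at SD 2.5 about 21% of the jin arm falls below zero on a scale from 0 to 10. The figures show a mechanism. They do not predict how many patients would be removed.

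**Conclusion.** The concern holds in this form: the removal rules in two sections conflict with an ITT analysis at all time points, because they end study participation for reasons that are wholly or partly related to outcome. If they are followed as written, the analysis of weeks 8 and 16, and of week 4 for earlier removals, must either depend on assumptions about missing values that cannot be tested or, if the repeated-measures model needs complete records, move towards the completers.

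Neither the size nor the direction of bias can be fixed from the article. Under the stated assumptions a true VAS difference of 2.0 would be seen as 1.84 in the mildest scenario, 1.70 with half of poor outcomes removed and 1.14 with all removed. Removal confined to one arm could inflate it instead. The textual conflict rests on none of these figures.

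**What to change.** Reconcile the Dropout criteria and Adverse events sections with the Statistical analysis section:

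1. State that meeting these criteria does not end study follow-up, and separate stopping treatment from leaving the study.
2. Clarify whether non-compliance and lack of efficacy must both be present, and what expected efficacy means, so that the reason can be recorded uniformly.
3. Continue the scheduled PD/PR, SEMG and scale assessments at weeks 4, 8 and 16 unless the patient withdraws consent for follow-up.
4. Analyse these data in the randomised arm.

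This changes data collection only; decisions on when treatment stops are left as they are. The cost is a short amendment, an instruction to the research team, and some follow-up visits that are already in the schedule. Recruitment began in April 2018, so the change helps only visits still to come: outcomes not collected at the time cannot be recovered after the trial ends.

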### Randomization, allocation concealment, and blinding

The eligible patients who meet the criteria will be randomly distributed to the *jin* acupuncture group and the pseudo acupuncture group with an allocation proportion of 1:1. A statistician who is not taking part in the clinical intervention will use SPSS 25.0 (IBM, Chicago, IL, USA) to generate a random allocation sequence. All of the random code information will be stored in sealed opaque envelopes by a well-trained specified assistant, who will randomize and inform the acupuncturists of the treatment assignments by phone. The allocation concealment procedure will not be exposed until the clinical trial is finished completely. Assessments and measurements of the participants will be carried out before and after the treatments and also at the follow-ups by different individuals of the research team. Researcher A will be responsible for the baseline assessment, administration of the questionnaire, and the measurement of cervical range of motion. Researcher B will be in charge of detecting the SEMG signal on the cervical extensor muscles. Researcher C will detect and record the pain degree (PD) and pain rate (PR) with the PainVision analyzer. Researcher D will be responsible for the analysis of SEMG data. A licensed acupuncturist who has worked for more than 18 years will perform acupuncture interventions on the patients, and patients will be treated in a shielded clinic room and deprived from knowing something about the pattern of treatment.

### Interventions

Patients in the *jin* acupuncture group will receive 12 sessions of acupuncture during a period of 4 weeks, implemented by finding the *gather* and *knot* of positive reaction, the points of both stress concentration and neurogenic stimulation in cervical extensor muscles according to TCM *jin* theory and modern biomechanical principles of soft tissue. Sterile and disposable filiform needles (Suzhou Acupuncture & Moxibustion Appliance Co. Ltd. Jiangsu, China) 40 mm in length and 0.30 mm in diameter will be inserted in accordance with the permissible depth and angle of the affected side acupoints until the *de qi* sensation is achieved. Meanwhile, acupuncture techniques of lifting-thrusting and twirling-rotating will be implemented to facilitate the arrival of *qi* involving a sensation of aching, numbness, heaviness, or distension around the acupoints. The needles will be retained for 25 min and stimulated every 8 min intermittently, with each acupoint being stimulated for 10 s. Participants in the pseudo acupuncture group will receive the sham acupuncture using filiform needles on points 5 cm apart away from the acupoints used in the *jin* acupuncture group. The skin will be punctured without any manipulation and stimulation for 25 min to avoid the *de qi* sensation, with the same sessions and courses as the *jin* acupuncture group. The baseline period is 0 to week 1 with one evaluation time before participating. The course of treatment and observation period will be three sessions a week totaling 12 sessions during the course. After 4 weeks of treatment, we will provide one evaluation session. The follow-up evaluation will be performed in the eighth and sixteenth weeks. The study schedule is shown in Fig. 2; the treatment details for each group are listed in Table 1.

**Fig. 2 Fig2:**
[figure not shown]
SPIRIT figure adopts PD and PR of PainVision analyzer, parameters of surface Electromyography (SEMG), short-form McGill Pain Questionnaire (SF-MPQ), range of motion (ROM) of the neck, Northwick Park Neck Pain Questionnaire (NPQ), Self-Rating Anxiety Scale (SAS), Self-Rating Depression Scale (SDS) for enrollment, interventions, and assessments

**Table 1 Tab1:** Treatment details for each group

Group	Acupoint/location (affected side)	Manipulation
*Jin* acupuncture	I. Stress concentration points a. In the midpoint of the connection between BL9 and BL10 b. In the midpoint of the connection between GB20 and SJ17 II. Positive reaction points c. GB8 d. In the midpoint of temporomandibular joint III. Nerve stimulation points e. The sensitive point of occipital protuberance of upper line of posterior occipital region f. Sensitive points on the posterior border of the upper third of the sternocleidomastoid muscle g. Sensitive spots in intertubercular sulcus of the second transverse process	a, b, f, g and GB34: Perpendicular insertion with 1.2 *cun* c: Oblique insertion with 0.8 *cun* toward the ipsilateral body d, e: Oblique insertion with 0.5 *cun* down Retaining needles for 25 min Lifting-thrusting, twirling, and rotating for *de qi* sensation
	Matching point: GB34	
Pseudo acupuncture	5 *cm* away from a, b, c, d, e, f, and g; 8 points in total	Retaining needles for 25 min only, pricking skin with no manipulation to avoid *de qi* sensation

Number of needle insertions per subject per session will be 8

### Outcome measures

#### Primary outcome measures

The following primary outcome measures will be used to evaluate the effectiveness at weeks 4, 8, and 16 after randomization, respectively, compared with the baseline.Pain degree (PD) and pain rate (PR): With a measurement accuracy of 0.1 μA, 0.3 ms pulse width, and 50 Hz pulse frequency, both indicators will be calculated using the current perception threshold (CPT) and pain equivalent current (PEC) with the PainVision analyzer according to the following formula [24, 25]:$$ PD=\frac{PEC- CPT}{CPT}\times 100\kern0.5em PR=\frac{PEC}{CPT} $$Surface electromyography (SEMG): With the patient in a prone position, a sticker will be placed on the affected side cervical extensor muscles (2 cm lateral to the posterior midline of the neck). The SEMG signal will be detected through an eight-channel module ME6000 biomonitor (Mega Electronics Ltd., Kuopio, Finland) as the operator successively applies 25% (maximum voluntary contraction, MCV), 50% MCV, and 100% MCV resistance, respectively, to the posterior occipital area. The system will automatically record and transmit the signal to generate the original image, and indicators of muscle fatigue including median frequency (MF), mean power frequency (MPF), average rectified value (ARV), and root mean square (RMS) will be calculated by Mega Win software for statistical analysis [26].

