**Design:**

This is a parallel-design, two-arm, patient-assessor blinded, randomized, sham-controlled clinical trial. A total of 166 patients with CEH aged from 18 to 70 will be recruited and assigned randomly into a *jin* acupuncture group and a pseudo acupuncture group at a 1:1 ratio; they will receive 12 sessions of real acupuncture and sham acupuncture for 4 weeks, respectively, during the study. The primary outcomes are pain degree (PD) and pain rate (PR) calculated by the PainVision analyzer, as well as parameters detected by surface electromyography (SEMG). The secondary outcomes will be measured with the short-form McGill Pain Questionnaire (SF-MPQ), range of motion (ROM) of the neck, the Northwick Park Neck Pain Questionnaire (NPQ), the 36-item short-form Health Survey (SF-36), the Self-Rating Anxiety Scale (SAS), and the Self-Rating Depression Scale (SDS). Clinical assessments will be evaluated at baseline and in the fourth week as well as in the eighth and sixteenth weeks. Adverse events will be noted and recorded for the safety evaluation.

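### PD, PR and several SEMG parameters at three visits are all primary under one 0.05 threshold, with no lead variable or visit named, so the chance of a false positive primary result is well above 5%

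*Protocol article*

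**What the plan says.** - **Which outcomes are primary.** The abstract (Design) states: "The primary outcomes are pain degree (PD) and pain rate (PR) calculated by the PainVision analyzer, as well as parameters detected by surface electromyography (SEMG"). Likewise, the Study design section makes the device measurements primary. Neither place ranks them.
- **SEMG indices.** Under Primary outcome measures, "median frequency (MF), mean power frequency (MPF), average rectified value (ARV), and root mean square (RMS) will be calculated". The list is introduced as inclusive, so four is a minimum.
- **Resistance levels.** The SEMG signal is taken while the operator "successively applies 25% (maximum voluntary contraction, MCV), 50% MCV, and 100% MCV resistance, respectively". The text does not say whether each index at each level is its own endpoint.
- **PD and PR.** Of these, "both indicators will be calculated using the current perception threshold (CPT) and pain equivalent current (PEC"). The formulas given are PD = 100 × (PEC − CPT)/CPT and PR = PEC/CPT.
- **Visits.** The "primary outcome measures will be used to evaluate the effectiveness at weeks 4, 8, and 16 after randomization", each against baseline. None is singled out.
- **Decision threshold.** Under Statistical analysis: "A two-sided value of *P* < 0.05 will be defined as the statistical significance".
- **Model.** The same section compares the continuous outcomes, primary ones included, between groups with a repeated-measures general linear model over all time points. It does not say which term or contrast from that model decides the result.

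**The concern.** The choice of primary variable and primary visit belongs in the protocol. This article is not silent on it: it states a primary set that spans several variables and three visits, and attaches one 0.05 threshold to all of them. Nothing in the document prevents a single favourable SEMG index from being reported as a positive primary result. The stated 5% then describes each test on its own and not the trial's conclusion.

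The sample size does not reveal a lead endpoint either. It is built on the VAS of the SF-MPQ, which the article lists as secondary. The Discussion promises strong evidence, and that promise depends on the primary test being fixed in advance.

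**Working it through.** The document states no familywise error rate to reproduce. Its only figure is 0.05 per test.

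**Step 1: distinct parameters.** From the article's formulas, PD = 100 × (PEC/CPT − 1) = 100 × (PR − 1). PD is an increasing linear function of PR, so a linear model or a rank test gives the same P value for both. They count once.

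- Resistance levels not separate endpoints: 1 + 4 = 5 distinct parameters.
- Each index a separate endpoint at each level: 1 + 4 × 3 = 13.
- Three visits tested separately: 5 × 3 = 15, or 13 × 3 = 39.

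**Step 2: independent tests.** The chance of at least one P < 0.05 with no true effect is 1 − 0.95^k.

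| k | Reading | Chance |
|---|---|---|
| 5 | one test per parameter, levels not separate | 22.6% |
| 13 | one test per parameter, levels separate | 48.7% |
| 15 | 5 parameters, each visit tested | 53.7% |
| 39 | 13 parameters, each visit tested | 86.5% |

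**Step 3: correlated tests, one repeated-measures test per parameter.** The document gives no correlations, so these are assumptions. Test statistics were simulated as multivariate normal, with PD independent of SEMG. The three values are the correlation within the MF–MPF and ARV–RMS pairs, between other index pairs, and between resistance levels (the last applies only to the 13-parameter case).

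| Assumed correlations | 5 parameters | 13 parameters |
|---|---|---|
| Low (0.5 / 0.1 / 0.3) | 21.4% | 44.6% |
| Moderate (0.8 / 0.2 / 0.5) | 19.0% | 37.3% |
| High (0.95 / 0.3 / 0.7) | 16.5% | 28.8% |
| Very high (0.95 / 0.5 / 0.8) | 16.0% | 25.5% |

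With the independent results as upper ends, the ranges are about 16–23% and 25–49%.

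**Step 4: each visit tested separately, correlated.**

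- 13 parameters: 44–79% across the four settings, with visit correlation 0.5 to 0.8.
- 5 parameters: 33–42% under the moderate and high settings, with visit correlation 0.5 to 0.7.

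**The case against.** A reader might infer that there are 14 primary parameters, that success on any one of 39 results suffices, and that a false positive primary result is therefore more likely than not. The documents do not support this stronger reading, for four reasons.

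- **The count.** PD and PR are one test, so 14 overstates the number. Even 13 assumes that each SEMG index is a separate endpoint at each resistance level, which the text does not say.
- **The visits.** The only analysis stated for the primary outcomes is a repeated-measures model across time points, not three separate tests. The wording of the outcome section allows a visit-by-visit reading, but that is one reading and not the stated plan. With one test per parameter, the chance stays below one half even for 13 independent tests (48.7%).
- **The success rule.** None is written. The threshold sentence defines significance in general terms. Silence on how results combine is not a rule that any one suffices. An all-must-succeed rule would keep the error at or below 5%, but it is not stated either.
- **The SAP.** It is not shown and may contain an adjustment or a named contrast. The supportable statement is that no control appears in this document.

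All four stand as limits on the size of the problem. They do not remove it. One model per variable still leaves at least five distinct primary tests, each at 0.05. The model also does not fix whether the group effect, the group-by-time interaction or one visit decides. Leaving an adjustment method to a SAP is normal; leaving the primary variable and visit unspecified in the protocol is not.

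**Conclusion.** The concern holds in a limited form. The article names PD, PR and at least four SEMG indices as primary at weeks 4, 8 and 16. It applies a two-sided 0.05 threshold and states no lead variable, visit, contrast, success rule or multiplicity control.

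If a significant result on any of these outcomes were taken as a positive primary finding, the error rate with one test per parameter would be about three to ten times the nominal 5% (16/5 to 49/5). Visit-by-visit testing raises it further, and the 86% figure is the extreme of 39 independent tests. These sizes rest on assumed correlations, on PD being independent of SEMG, and on how resistance levels and visits are treated. No case computed comes near 5%. The width of the range itself shows that the primary test has not been fixed.

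**What to change.** Before unblinding, by dated amendment and registry update:

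1. Drop PR as a separate primary, because it repeats PD.
2. Name one primary variable, one time point and one between-group contrast from the repeated-measures model, tested at two-sided 0.05. PD at week 4, *jin* against pseudo acupuncture, is one example. Make the other visits and the SEMG indices secondary.
3. If SEMG must stay primary, fix one index at one resistance level and test it with PD in a fixed sequence or with Holm.
4. State that the sample size rests on the SF-MPQ VAS, a secondary outcome. Then either align the primary with the variable used for sizing, or say that power for the chosen primary was not calculated. Choosing PD without this statement would leave the primary with no stated power basis.

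The cost is an amendment and a registry update; no additional measurements are required. The downside is that SEMG results and the later visits lose confirmatory status.
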